### Sample size

2.7

This study aims to determine whether HT048 and HT077 is superior to placebo in reducing the change in percent body fat as measured by DXA at 12 weeks after the baseline measurement. The sample size has been estimated based on a previous study that evaluated the efficacy of an herbal extract powder for body fat reduction in overweight adults with a BMI of 25.0 to 29.9 kg/m^2^.^[23]^ The mean changes in percent body fat after the 12-week administration period are hypothesized to be 2.2% and 0.5% in the treatment and placebo groups, respectively, and the pooled standard deviation is hypothesized to be 2.14. Therefore, 25 participants in each group are needed to achieve a statistical power of 80% with a 2-sided significance level of 5%. To increase the power of the study, the sample size will be increased by 28%, with 32 participants in each group. Considering a drop-out rate of 20%, a total of 120 participants, 40 in each group, will be included in this study.

### Statistical analysis

2.8

The efficacy outcome data will be analyzed by using both intention-to-treat and per-protocol population. The intention-to-treat population will comprise all randomized participants and the per-protocol population will be composed of participants whose primary efficacy assessments were performed according to the protocol without major protocol violations, such as unmet inclusion/exclusion criteria or the use of prohibited medication. Participants whose compliance to treatment is less than 80% will be excluded from the per-protocol population. The safety outcome data will be analyzed by using a safety population, which will include participants who receive treatment at least once and have at least 1 safety assessment after treatment. Missing data will be replaced using the last observation carried forward method.

Continuous variables will be described as mean, median, standard deviation, and range (minimum and maximum), and categorical variables will be described as frequency and percentage. Analysis of covariance with the baseline measurements as a covariate will be performed to examine inter-group differences in the primary and secondary endpoints. Continuous variables will be compared by using an independent *t* test or Wilcoxon rank-sum test between the treatment and placebo groups, depending on normality of the distribution. In addition, differences within groups before and after the intervention will be compared by using a paired *t* test or Wilcoxon signed-rank test. Categorical variables will be presented as the frequency and percentage and compared by using either the Chi-square or Fisher exact test. Adverse events will be classified by the Common Terminology Criteria for Adverse Events from the National Cancer Institute (ver. 4.0). Probability values of <.05 with 2-tailed tests will be considered significant. The statistical analysis will be performed with SPSS Statistics software version 25 (IBM, Chicago, IL). No interim analyses will be performed.

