### Outcome measures and endpoints

2.6

DXA will be used to assess body fat mass and percent body fat at baseline and week 12 as the primary outcome measure. In addition, body fat mass and percent body fat will be measured by BIA at baseline and weeks 4, 8, and 12. DXA and BIA are representative methods for assessing body composition, and the correlation between the 2 measurements for body fat mass and percent body fat are generally known to be good in both sexes.^[19,20]^ Abdominal CT will be used to measure visceral fat area, subcutaneous fat area, total abdominal fat area, and visceral fat/subcutaneous fat area ratio at baseline and week 12. CT scanning will be performed between the fourth and fifth lumbar vertebrae. With high accuracy, CT is considered as the reference method for measuring visceral and subcutaneous fat.^[21]^ Body weight and BMI will be measured at baseline and weeks 4, 8, 12, and 16. Waist circumference, hip circumference, and waist circumference/hip circumference ratio will be assessed at baseline and weeks 4, 8, and 12. According to the World Health Organization guidelines, waist circumference will be measured at the midpoint between the lower margin of the last palpable rib in the midaxillary line and the top of the iliac crest, and hip circumference will be measured at the largest circumference of the buttocks.^[22]^ Serum lipids (total cholesterol, triglyceride, high density lipoprotein cholesterol, and low-density lipoprotein cholesterol) and adipocytokines (leptin and adiponectin) concentrations will be assessed at baseline and week 12.

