The primary efficacy endpoint is the change in body fat mass and percent body fat measured by DXA at week 12 from the baseline. The secondary efficacy endpoints are as follows:(1)the change in body fat mass and percent body fat measured by BIA at weeks 4, 8, and 12 from the baseline;(2)the change in visceral fat area, subcutaneous fat area, total abdominal fat area, and visceral fat/subcutaneous fat area ratio measured by abdominal CT at week 12 from the baseline;(3)the change in body weight at weeks 4, 8, and 12 from the baseline;(4)the change in BMI at weeks 4, 8, and 12 from the baseline;(5)the change in waist circumference, hip circumference, and waist circumference/hip circumference ratio at weeks 4, 8, and 12 from the baseline;(6)the change in blood lipids (total cholesterol, triglyceride, high density lipoprotein cholesterol, and low-density lipoprotein cholesterol) concentrations at week 12 from the baseline;(7)the change in serum leptin and adiponectin concentrations at week 12 from the baseline;(8)the change in body weight at week 16 from week 12; and(9)the change in BMI at week 16 from week 12.

Safety will be assessed on the basis of adverse events reported by participants or the principal investigator, abnormal laboratory results (hematology, biochemistry, and urinalysis), vital signs, and physical examination findings. Laboratory tests will be performed at screening, baseline, and week 12. Measurements of vital signs and physical examination will be performed at every visit.

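### With only one post-baseline DXA scan, last observation carried forward gives every participant without a week-12 scan a change of exactly zero and distorts the ITT estimate of the primary endpoint

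*Protocol article*

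**What the plan says.** All places are in the protocol article.

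- Section 2.6 (Outcome measures and endpoints) fixes the schedule: "DXA will be used to assess body fat mass and percent body fat at baseline and week 12 as the primary outcome measure". Abdominal CT, serum lipids, leptin and adiponectin are also taken only at those two times. BIA and waist and hip circumference are taken at baseline and weeks 4, 8 and 12; weight and BMI also at week 16.
- The same section defines the endpoint: "The primary efficacy endpoint is the change in body fat mass and percent body fat measured by DXA at week 12 from the baseline".
- Section 2.8 (Statistical analysis) sets the populations: "The efficacy outcome data will be analyzed by using both intention-to-treat and per-protocol population", and "The intention-to-treat population will comprise all randomized participants". Neither set is named as primary.
- Section 2.8 gives one rule for incomplete data, with no restriction by endpoint: "Missing data will be replaced using the last observation carried forward method". The model is: "Analysis of covariance with the baseline measurements as a covariate will be performed to examine inter-group differences in the primary and secondary endpoints".
- Section 2.7 (Sample size) assumes changes in percent body fat "hypothesized to be 2.2% and 0.5% in the treatment and placebo groups, respectively", with a pooled SD of 2.14. It ends: "Considering a drop-out rate of 20%, a total of 120 participants, 40 in each group, will be included in this study".

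The text describes no DXA scan at early termination and no sensitivity analysis for missing data. Table 1 is not available to us.

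**The concern.** Carrying an observation forward has some content when there are interim visits. DXA has none, so the only value to carry is the baseline scan and the imputed change is zero by construction. Zero is neither of the mean changes that Section 2.7 expects. Section 2.7 sizes the trial for a 1.7-point difference in 32 participants per group after drop-out; the ITT analysis in Section 2.8 would mix those participants with up to 8 per group at zero.

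At stake are the estimate and interval for the primary endpoint. The rule cannot be relied on to be conservative: its bias depends on how many scans each arm loses. The reasons for stopping in Section 2.4 (for example a serious adverse event, or use of something that affects body weight) could plausibly differ by arm. The rule also leaves unused the interim BIA and weight values, although Section 2.6 itself describes the correlation between BIA and DXA as good.

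**Working it through.** **Inputs.** From Section 2.7: mean reductions of 2.2 and 0.5 points, SD 2.14, two-sided 5% level, 80% power, 25 then 32 then 40 per group, 20% drop-out. Assumed here: all drop-out precedes the week-12 scan; it is unrelated to outcome; unequal rates of 10% and 30% illustrate a range, since the plan gives only 20% overall. Section 2.7 gives no planning figures for fat mass, so the size is shown for percent body fat.

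**The plan's own figure.** n = 2 × (1.96 + 0.84)² × 2.14² / 1.7² ≈ 24.9, so 25 per group. 25 × 1.28 = 32, and 32 / 0.8 = 40. The stated sample size is reproduced (normal approximation; the exact t calculation needs 26).

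**Effect of the rule.** If a share d of an arm with mean reduction m is set to zero:

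- arm mean = (1 − d)m
- arm variance = (1 − d)SD² + d(1 − d)m²
- SE of the difference = √((V_active + V_placebo)/40)

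At d = 0.2 in both arms:

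- difference = 0.8 × 2.2 − 0.8 × 0.5 = 1.36
- V_active = 0.8 × 4.580 + 0.16 × 4.84 = 4.438 (SD 2.107)
- V_placebo = 0.8 × 4.580 + 0.16 × 0.25 = 3.704 (SD 1.924)
- SE = √(8.142/40) = 0.451
- power = Φ(1.36/0.451 − 1.96) = 85%

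With the 32 observed scans per arm alone: difference 1.70, SE = 2.14 × √(2/32) = 0.535, power = Φ(1.70/0.535 − 1.96) = 89% (88% by the t distribution).

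**Coverage.** The shift is 1.70 − 1.36 = 0.34, and 0.34/0.451 = 0.754 standard errors. Coverage of 1.70 is Φ(1.96 − 0.754) − Φ(−1.96 − 0.754) ≈ 88%.

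**Other scenarios.**

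| True reductions (active / placebo) | Drop-out (active / placebo) | Expected ITT difference | True difference |
|---|---|---|---|
| 2.2 / 0.5 | 10% / 10% | 1.53 | 1.70 |
| 2.2 / 0.5 | 30% / 30% | 1.19 | 1.70 |
| 2.2 / 0.5 | 30% / 10% | 1.54 − 0.45 = 1.09 | 1.70 |
| 2.2 / 0.5 | 10% / 30% | 1.98 − 0.35 = 1.63 | 1.70 |
| 0.5 / 0.5 | 20% / 20% | 0 | 0 |
| 0.5 / 0.5 | 10% / 30% | 0.45 − 0.35 = 0.10 | 0 |
| 2.2 / 2.2 | 10% / 30% | 1.98 − 1.54 = 0.44 | 0 |

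**Simulation check.** 10,000 trials per scenario, ANCOVA with baseline as covariate, baseline generated independently of the change. At 20% in both arms the mean estimate was 1.36, the SD of the estimates 0.455, the mean model SE 0.452, coverage of 1.70 88% and power 84% (87% from observed scans). With exactly 8 lost per arm in every trial, coverage was 90%. At 30% / 10%, power was 66%. Type I error was 5% with equal drop-out. With 10% / 30% it was 6% for a common reduction of 0.5 and 16% for a common reduction of 2.2.

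**The case against.** Five points can be made for the plan.

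1. A reader might infer that the standard error is wrong in itself and produces false positives. The calculations do not support that. The model SE matches the actual spread of the estimator (0.452 against 0.455), the bias alone explains the loss of coverage, and type I error stays near 5% with equal drop-out. What stands is narrower: 0.451 read as precision about the 12-week effect is too favourable, because 32 scans per arm support only 0.535.

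2. A reader might take ITT to be the declared primary analysis. Section 2.8 does not say so, and a per-protocol analysis is planned beside it. That analysis requires the primary assessments to have been performed, so it contains none of these zeros, and a gap between the two would be visible. It is no remedy, because it also removes major violators and anyone below 80% compliance.

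3. A reader might apply the zero to all drop-outs. People lost between weeks 12 and 16 already have the scan, so 8 per arm is an upper limit under the planned rate. A scan at early termination cannot be fully ruled out without Table 1.

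4. The plan does not say that drop-outs would have shared the completers' mean changes. That is an assumption of this check. If their mean change at week 12 were truly zero, the bias would vanish; nothing in the article argues that it would be.

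5. At the planned 20%, power stays above 80%, and the worst false-positive figure needs both an assumed imbalance and a placebo reduction of 2.2 that the plan does not expect. This is correct and limits the size of the point. It does not rescue a rule whose bias depends on who happens to leave.

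**Conclusion.** The point holds for the ITT analysis of the primary endpoint, and in the same way for CT, lipids and adipocytokines. Followed as written, the rule is baseline carried forward.

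On the plan's figures, with 20% lost in each arm before week 12 and unrelated to outcome, the expected difference falls by 0.34, a fifth of the planned effect (0.34/1.70). Equal drop-out only attenuates. Unequal drop-out can hide much of a real effect or create one where none exists; those sizes rest on assumed rates.

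The documents do not support calling the smaller standard error a second, separate defect, or saying that the plan contradicts its own assumptions, since it is silent on what drop-outs' week-12 values would be. The stated rule should be replaced before unblinding: it governs the main efficacy estimate, and better information is already being collected.

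**What to change.** Replace the single missing-data sentence in Section 2.8.

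- **Endpoints with one post-baseline measurement (DXA, CT, lipids, adipocytokines), ITT set:** ANCOVA after multiple imputation from a small model containing treatment arm, baseline value and the available post-baseline BIA or weight values. It should stay small: about 32 observed scans per arm will not support many closely correlated predictors. Participants who leave before week 4 contribute only arm and baseline values.
- **Repeatedly measured endpoints (BIA, weight, BMI, waist and hip):** a mixed model for repeated measures over weeks 4, 8 and 12.
- **Sensitivity:** keep baseline carried forward, labelled as such, and optionally add a placebo-based imputation, because the main analysis would assume that missingness is explained by the data in the model.

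The cost is wording, a little programming and a somewhat wider interval. No further participants, visits or measurements are needed.

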### Eligibility criteria

2.2

Participants who meet all the following criteria will be included.Men and women aged ≥19 and <60 years,BMI of 25 to <30 kg/m^2^,Participants who voluntarily decide to participate and sign the informed consent after being provided an explanation of this trial.

Participants who fall under any of the following conditions will be excluded.History of hypersensitivity to drugs or food ingredients,Participation in a commercial weight loss program or clinical trial for obesity within the last 3 months,Taking drugs or diet foods that affect their weight within 3 months before screening,Intentional weight loss of at least 5% within 3 months before screening,Undergone surgery, such as gastroplasty and intestinal resection, to lose weight within 6 months before screening,Endocrine diseases such as hypothyroidism and Cushing syndrome,Severe cerebrovascular disease (cerebral infarction, cerebral hemorrhage, etc), heart disease (angina pectoris, myocardial infarction, heart failure, arrhythmia in need of treatment), and lung disease (chronic obstructive pulmonary disease, etc) within the last 6 months. (However, those who are clinically stable may participate in the trial at the investigator's discretion),Serious dysfunction of the liver (alanine and aspartate aminotransferase levels of 2.5 times the upper limit of normal) or kidney (creatinine >2.0 mg/dL),Uncontrolled hypertension (blood pressure ≥160/100 mm Hg),Fasting blood glucose ≥126 mg/dL or random blood glucose ≥200 mg/dL, or diabetic patients taking oral hypoglycemic agents or insulin,Malignant tumor diagnosed within 3 years before screening,Complaint of severe gastrointestinal symptoms such as heartburn and indigestion,Psychologically significant medical history or current disease (schizophrenia, epilepsy, anorexia, bulimia, etc), or a history of alcohol or drug abuse,Determined to be unable to exercise because of musculoskeletal disorders,Pregnant or lactating women, or women of childbearing age who do not agree to use contraception during the trial,Participants who are deemed unable to comply with the test requirements or otherwise deemed unsuitable according to the investigator's opinion.

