### Harms

2.10

All adverse events will be monitored and recorded, irrespective of causality. The principal investigator will evaluate the severity of symptoms and the causal relationship to the investigational product. If a serious adverse event occurs, it will be reported to the Institutional Review Board and sponsor within 24 hours, and the participation will be discontinued. Participants will be compensated for medical expenses related to injuries that are confirmed to be caused by the trial procedure or investigational products.

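### The carry-forward rule is not limited to efficacy, so read literally it fills a missing week-12 laboratory safety result with a pre-treatment value and records no change from baseline

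*Protocol article*

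**What the plan says.** Section 2.8 (Statistical analysis) first defines the two efficacy populations. It then assigns the safety outcomes to a population of their own and sets its membership broadly, as a group "which will include participants who receive treatment at least once and have at least 1 safety assessment after treatment". The next sentence, which closes the paragraph, is the missing-data rule: "Missing data will be replaced using the last observation carried forward method". It names no endpoint, population or type of data.

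Section 2.6 (Outcome measures and endpoints) lists among the safety outcomes "abnormal laboratory results (hematology, biochemistry, and urinalysis), vital signs, and physical examination findings". The schedules differ within that list. For the laboratory: "Laboratory tests will be performed at screening, baseline, and week 12". For the others: "Measurements of vital signs and physical examination will be performed at every visit".

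Two other places bear on the point. Section 2.2 (Eligibility criteria) excludes serious liver dysfunction, with the limit given as "alanine and aspartate aminotransferase levels of 2.5 times the upper limit of normal". Section 2.10 (Harms) says of a serious adverse event that "it will be reported to the Institutional Review Board and sponsor within 24 hours, and the participation will be discontinued".

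**The concern.** Carrying forward the last observation needs an earlier observation that is informative about the missing one. For laboratory safety the schedule provides none: week 12 is the only planned draw after the first dose. When it is missing, the last scheduled observation was taken before any product was given. It carries no information about what the product did to liver, kidney or blood values, yet under the rule it would stand in the table as the week-12 result with a change of zero.

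The safety population does not remove these participants. Someone who attends week 4 and then leaves has had vital signs and a physical examination after starting treatment, which is enough to be included.

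At stake is the laboratory part of the safety evidence. The article describes the trial as first-in-human, lists safety among its secondary objectives, and plans neither an interim analysis nor a data monitoring committee, so the final tables matter. Missing results may also be related to harm, because a serious adverse event ends participation.

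**Working it through.** **Inputs.** From section 2.7: 40 randomised per group, 32 expected to remain, drop-out 20%. From section 2.6: laboratory tests at screening, baseline and week 12. From section 2.8: the unrestricted rule and the definition of the safety population. The documents give no laboratory abnormality rates, so every rate below is an assumption.

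**The plan's own figures.** With a difference of 2.2 − 0.5 = 1.7, SD 2.14, two-sided 5% and 80% power:
- n = 2 × (1.960 + 0.842)² × 2.14² / 1.7² ≈ 24.9, so 25 per group.
- 25 × 1.28 = 32.
- 32 / (1 − 0.20) = 40 per group, 120 in total.

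These reproduce and are not affected by this point. They supply the 40 and the 32.

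**Following the rule for one participant.** Take someone who attends week 4, then leaves, with no unscheduled test.
1. In the safety population? Yes: treated, with a later safety assessment.
2. Week-12 laboratory result? Missing.
3. Last laboratory observation? Baseline, or screening if baseline is missing.
4. Value entered at week 12? That pre-treatment value, with a change of zero.

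**How many.** At most 40 × 0.20 = 8 per group, or 24 of 120. Reaching 8 requires that the full 20% drop-out occurs, that every leaver stays in the safety population, and that none has an on-treatment test.

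**Effect on a rate.** Let m be the share with a missing week-12 result, q the true on-treatment abnormality rate (taken as the same in leavers and completers) and b the share of carried values that are abnormal. Then

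recorded rate = (1 − m) × q + m × b.

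| m | b | q = 5% | q = 10% | q = 20% |
|---|---|---|---|---|
| 20% | 0% | 4.0% | 8.0% | 16.0% |
| 20% | 2% | 4.4% | 8.4% | 16.4% |
| 5% | 0% | 4.75% | 9.5% | 19.0% |

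In counts, with m = 20%, b = 0 and an assumed 4 abnormal results among 32 observed: 4/32 = 12.5% is shown as 4/40 = 10.0%.

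**Zero events.** The one-sided 95% upper limit is 1 − 0.05^(1/n).
- n = 32: 1 − 0.05^(1/32) = 8.9%.
- n = 40: 1 − 0.05^(1/40) = 7.2%.

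The plan does not call for this limit. It is used here only to show the precision gained from 8 results that were never observed.

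**If leaving is related to harm.** Assume 5% abnormal in completers and 25% in leavers, with m = 20% and b = 0.
- True rate: 0.8 × 5% + 0.2 × 25% = 9%.
- Recorded under the rule: 0.8 × 5% + 0.2 × 0% = 4%.
- Observed results only: 5%.

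Observed-only reporting also falls short of 9% here. It does not add the further dilution, and it leaves the missing results visible.

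**The case against.** The strongest reply is that no sentence says the rule will be applied to laboratory safety data. The rule closes a paragraph that opens with the efficacy populations, and it may have been written with efficacy in mind. The full protocol and any analysis plan are not shown and may narrow it. This lowers certainty about what will be done. It does not change what the article states: the same paragraph distinguishes efficacy from safety outcome data, then gives a rule with no such limit immediately after the safety population. The point rests on that stated rule set against the stated schedule, not on a detail left out.

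A reader might infer that a leaver would be counted as safe. The documents do not support that. The carried value is recorded as unchanged from baseline, and it looks normal only if the baseline value was normal. Entry excludes serious liver or kidney dysfunction, not milder abnormalities, so some carried values could be abnormal. The article does not say how a carried value would be classified.

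A reader might also infer that harm in people who stop would disappear from the results. That is not supported either. Section 2.10 records all adverse events whatever their cause, and they are reported separately from the laboratory tables.

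The objection that 8 of 40 is not a forecast stands. The 20% was used to size the primary endpoint. Some leavers may have no safety assessment after treatment and drop out of the population, and others may have an unscheduled test, which would be carried instead. The schedule table is not visible, so any withdrawal testing it lists cannot be checked.

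Finally, the problem does not extend equally to all safety data. Vital signs are taken at every visit, so after week 4 a carried value is an on-treatment one. Adverse events have no scheduled value to carry.

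**Conclusion.** The concern holds for laboratory safety data. As written, the missing-data rule, the single post-treatment laboratory draw and the broad safety population together put a pre-treatment value in place of a missing week-12 result and record no change. This tends to dilute rates of treatment-emergent laboratory abnormality.

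The size is modest if missingness is unrelated to harm: 12.5% shown as 10.0% in the upper-case illustration, and 8.9% shown as 7.2% for the upper limit with no events. It can be larger if leaving is related to harm: 9% recorded as 4% under the assumed rates. These figures assume that all 8 leavers per group stay in the safety population with normal baseline values and no on-treatment test. Fewer missing results, or some abnormal baseline values, reduce the dilution. Confidence is medium, because the full protocol or analysis plan may restrict the rule.

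**What to change.** Amend the missing-data sentence in section 2.8 so that imputation applies to efficacy endpoints only. At the least, state that no pre-treatment value is carried into safety data. Add that laboratory safety is reported on observed post-baseline results, scheduled or unscheduled, with participants who have such a result as the denominator, and that each laboratory table shows by arm how many in the safety population have none. No change is needed for adverse events, which have no scheduled value to carry.

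The cost is a sentence or two of text and smaller laboratory denominators, about 32 instead of 40 per group if the full 20% drop-out occurs. Unscheduled tests may be prompted by symptoms, so they are best identified as such in the tables. The sample size is unchanged.

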### Randomization and blinding

2.5

Participants determined to be eligible for this study will be randomly assigned to the HT048, HT077, or placebo groups in a 1:1:1 ratio using a computerized block randomization method. An independent statistician will generate the randomization sequence number and the block size will not be disclosed to the investigator for allocation concealment. Participants will be assigned a randomization number consecutively in the order in which they are enrolled and will receive the investigational product labeled with the same randomization number throughout the trial. The packaging and labels of investigational products for the 3 groups will remain the same for blinding purposes. Participants and all research personnel will be blinded to the assignment. The randomization sequence will be concealed in sealed opaque envelopes and will not be disclosed to the investigator until the end of the study, except when inevitable, such as when serious adverse events occur. If a code break occurs, the investigator will notify the contract research organization and the sponsor immediately and record the date and reason for the code-break in the case report form.

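### The ANCOVA adjusts for the baseline value only; prespecifying sex as a factor would be a small, uncertain but nearly free gain in precision and robustness

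*Protocol article*

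**What the plan says.** Section 2.8 (Statistical analysis) gives one model for comparing the groups on all primary and secondary endpoints: "Analysis of covariance with the baseline measurements as a covariate will be performed". No further covariate is named there.

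Section 2.6 (Outcome measures and endpoints) defines what that model must serve first: "The primary efficacy endpoint is the change in body fat mass and percent body fat measured by DXA at week 12 from the baseline".

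Section 2.2 (Eligibility criteria) admits both sexes, "Men and women aged ≥19 and <60 years", and sets no sex quota. Section 2.5 (Randomization and blinding) allocates participants "in a 1:1:1 ratio using a computerized block randomization method" and names no stratification factor.

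The only other mention of adjustment is in the Discussion. It makes adjusted analyses conditional on differences seen in the diet and activity surveys, and sex is not mentioned.

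Section 2.7 (Sample size) rests on percent body fat, with mean changes "hypothesized to be 2.2% and 0.5% in the treatment and placebo groups, respectively", and "the pooled standard deviation is hypothesized to be 2.14". It takes no credit for any covariate.

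**The concern.** Body fat is an endpoint on which the sexes plausibly differ, and sex can be recorded for every participant. The baseline value stands in for sex only in part. If men and women differ clearly in baseline percent body fat, a single pooled slope blends the between-sex relation with the within-sex relation, and it can fit both poorly.

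Two things follow. Any sex difference in the 12-week change that baseline does not explain stays in the residual error and costs some power. And if the arms differ in sex mix by chance, the estimate moves by whatever part of that difference the baseline term does not absorb. With 32 to 40 participants per arm, a visible chance imbalance is not rare.

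**Working it through.** **1. The plan's own figures.** Inputs from section 2.7: difference 2.2 - 0.5 = 1.7 points, SD 2.14, two-sided 5%, power 80%. The normal-approximation formula n = 2 × SD² × (z0.975 + z0.80)² / difference² gives 25 per arm. Then 25 × 1.28 = 32, 32 / 0.80 = 40, and 3 × 40 = 120. All stated figures reproduce. Power at 32 per arm is 88.8% by the normal approximation and 87.9% by the two-sample t calculation, with no covariate gain assumed.

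**2. Residual variance with and without sex (percent body fat).** The documents give none of the sex-specific inputs, so these are assumptions: share of women p = 0.5 to 0.7; baseline gap, women minus men, D = 8 to 10 points; within-sex baseline SD s = 4; within-sex slope of change on baseline b = 0 to -0.2; sex difference in mean change d = -1 to +1 point. The total variance of change is V = 2.14² = 4.58.

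- Baseline only: V - cov² / Var(baseline), with cov = b·s² + p(1-p)·D·d and Var(baseline) = s² + p(1-p)·D².
- Baseline and sex: V - b²·s² - p(1-p)·d².

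Four cases at p = 0.5:

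| D | b | d | Baseline only | Baseline and sex | Cut |
|---|---|---|---|---|---|
| 8 | 0 | 0 | 4.58 | 4.58 | 0% |
| 8 | 0 | +1 | 4.58 - 2.0²/32 = 4.45 | 4.58 - 0.25 = 4.33 | 2.8% |
| 8 | -0.2 | -1 | 4.58 - 5.2²/32 = 3.73 | 4.58 - 0.64 - 0.25 = 3.69 | 1.2% |
| 10 | -0.2 | +1 | 4.58 - 0.7²/41 = 4.57 | 3.69 | 19.2% |

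Over the whole grid the cut runs from 0 to 19%, with a median of about 2% and a middle half of about 0.5-5%. The sign of d matters. If d is restricted to 0 to +1, where the sex difference works against the negative slope, the median is about 4.6% and the middle half about 2-9%. If d is restricted to -1 to 0, the maximum is 9%.

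**3. Effect on power.** Take 2.14 as the residual SD before sex is added and scale it by √(1 - cut). The two-sample t power at 32 per arm is:

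| Cut in variance | Power |
|---|---|
| 0% | 87.9% |
| 2% | 88.5% (+0.6) |
| 5% | 89.4% (+1.6 before rounding) |
| 10% | 90.9% (+3.1 before rounding) |

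The cost is one degree of freedom. With 96 completers, three arm means and one slope, 96 - 4 = 92 residual degrees of freedom become 91.

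**4. Chance imbalance.** Treat the number of women in each arm as binomial(n, 0.5), where 50% women is an assumption. The chance that one active arm and placebo differ in the share of women is:

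| Difference | n = 32 | n = 40 |
|---|---|---|
| 15 points or more | 26% | 22% |
| 20 points or more | 10% | 9% |

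**5. What a 20-point imbalance does.** With d = +1, the shift before baseline adjustment is 0.20 × 1 = 0.2 points, which is 0.2 / 1.7 = 12% of the planned effect. The planned model adjusts for baseline, so the relevant shift is 0.20 × (d - β·D), with pooled slope β = cov / Var(baseline). At p = 0.5 this is 0.20 × (1 - 0.061 × 10) = 0.08 for b = 0 and D = 10. It is 0.20 × (1 + 0.0375 × 8) = 0.26 for b = -0.2 and D = 8. Baseline adjustment may therefore remove part of the shift or, with a steep negative within-sex slope, add to it.

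**The case against.** The strongest reply is that nothing here is wrong. ANCOVA on change with the baseline value as covariate is a standard and valid analysis of a randomised trial. A pooled slope that fits the sexes poorly does not bias the randomised comparison, and chance sex imbalance is already allowed for in the standard error and the type I error. All of that stands. A reader might infer that the primary test is biased or the trial underpowered. The documents do not support this: the sample size uses SD 2.14 with no covariate gain and was raised from 25 to 32 per arm.

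A second reply is that further covariates may be named in the full protocol or analysis plan, and that the article is only silent on stratification and does not exclude it. This stands as a limit on what can be claimed: the article names no stratification factor, and no more than that is known. It does not dispose of the point, because the article does state the covariate, and the suggestion concerns that stated choice.

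A third reply is that the benefit is wholly assumed. It is, and the lower bound is zero. A reader might also infer a typical variance cut of 2-9%, but that needs the sex difference in change to run in one direction only, and the documents give no ground for excluding the other. Pairing the 22-26% chance of imbalance with the 0.2-point shift would also mislead. That chance belongs to a 15-point imbalance, while the shift belongs to a 20-point one and ignores the baseline adjustment.

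**Conclusion.** The point holds as a minor, optional improvement in efficiency and robustness. It is not an error or a contradiction. For percent body fat, the likely gain is a cut of a few percent in residual variance, worth roughly 0 to 1.6 power points at 32 per arm over most of the assumed range. A material gain needs a cut of about 10% or more, which occurs only towards one corner of the grid. Protection against chance imbalance is the other benefit, and an imbalance of 20 points against placebo should be seen in about one trial in ten for a given active arm if half the participants are women.

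Every sex-specific input is an assumption. A reader might extend the gain to body fat mass, the other primary measure. No calculation supports that, because the documents give neither a sex gap nor an SD for it.

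**What to change.** Before unblinding, state in section 2.8 and in the analysis plan that the primary and secondary endpoints will be analysed by ANCOVA with treatment arm and sex as factors and the baseline value as covariate, using the same model for both DXA measures. If the full protocol or analysis plan already says this, nothing further is needed.

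The cost is one sentence and one of about 92 residual degrees of freedom. Sample size and randomisation stay as they are, and no data are needed beyond each participant's sex. Timing is the only real constraint: a covariate chosen after the allocation is known would not carry the same credibility.
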